|  |  |  |  |  |  |  |  |  |  |
|  |  |  |  |  |  |  |  |  |  |
|  |  |  |  |  |  |  |  |  |  |
|  |  |  |  |  |  |  |  |  |  |
|  |  |  |  |  |  |  |  |  |  |
|  | [Three months after enrollment]  Primary endpoint: Number of hospitalizations, number of hospital days, and number of unscheduled outpatient visits in the past 3 months  Secondary endpoints: SGRQ score, EQ-5D index, SCAQ responses, respiratory function test, and 6-min walk test | | | | | | | |  |
|  |  |  |  |  |  |  |  |  |  |
|  |  |  |  |  |  |  |  |  |  |
|  |  |  |  |  |  |  |  |  |  |
|  | [Expected effects of the intervention]  The tele-nursing intervention program is expected to ameliorate the self-management behavior of the intervention group and to significantly improve the primary and secondary endpoints compared with the control group | | | | | | | |  |
|  |  |  |  |  |  |  |  |  |  |
|  |  |  |  |  |  |  |  |  |  |

- 1. **Objective**

The purpose of this randomized, controlled trial is to evaluate the effect of a tele-nursing intervention program utilizing Information and Communication Technology (ICT) on the prevention of acute exacerbations in patients with chronic respiratory failure receiving noninvasive positive-pressure ventilation (NPPV) in home care.

- 1. **Participants**

We included patients aged at least 20 years, with chronic respiratory failure, receiving NPPV, attending the outpatient Department of Respiratory Medicine at Tohoku University Hospital and cooperating institutions, without cognitive impairment, and who provided informed consent for study participation.

- 1. **Number of planned cases and study period**

(1) Number of planned cases

Based on previous literature, the average number of visits to the emergency department due to acute exacerbation of chronic respiratory disease in patients who use and do not use NPPV is 2.4 and 1.6 times/year, respectively; hence, we assume that the number of visits will improve by 1.0 time/year. The significance level will be 5%, the power will be 80%, and the standard deviation of the number of visits assumed to reduce the occurrence of acute exacerbations will be 1.0 visit/year. In addition, the proportion of included patients who drop out in the middle of the study is assumed to be 10% of the total number of patients; in addition, the intervention and control groups will comprise 17 patients each. Therefore, the planned number of cases for this study is 34.

(2) Research period

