# Methods and duration of the study

# Research design

1. Research design

This is a randomized, controlled trial conducted on two groups of patients: an intervention group using an ICT-based tele-nursing intervention program for patients with chronic respiratory failure receiving NPPV at home (in addition to usual care) and a control group receiving usual care.

1. Rationale for setting up the study design

The purpose of this study is to evaluate the effectiveness of a tele-nursing intervention program for patients with chronic respiratory failure receiving NPPV. To this end, the study design was set up as a randomized, controlled trial based on the hypothesis that the group of patients who undergo the tele-nursing intervention program (intervention group) will have fewer temporary outpatient visits (percentage and number of visits) due to acute exacerbations during the intervention period than the group of patients who receive only usual care (control group).

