# Secondary endpoints

Secondary endpoints included the St. George's Respiratory Questionnaire (SGRQ) score, developed as a specific health-related QOL measure for respiratory diseases; Euro Qol 5 Dimension (EQ-5D) index, a QOL assessment instrument used to calculate quality-adjusted life years in the economic evaluation of medical technology; and Self-Care Capacity Questionnaire score, a measure of the degree of patient self-care. respiratory function measurements; and 6-min walk test distance will be collected at baseline and 12 and 24 weeks after enrollment. In addition, as an objective measure of physical activity, the average number of steps taken and amount of activity will be collected from an activity meter at 12 and 24 weeks after enrollment.

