# Statistical analyses

# Statistical analysis methods

Data on basic participant characteristics will be examined for normality using the Kolmogorov-Smirnov test, and the differences between the means or medians for the data in the intervention and control groups will be compared using the *t*-test, based on the normality of the data. Fisher's exact test will be used to compare the primary endpoints of temporary outpatient visit and readmission rates between groups, and student *t*-test will be used to compare the number of temporary visits and readmissions between groups. Paired *t*-tests will be used to compare changes in secondary endpoints at baseline, 12 weeks after enrollment and intervention initiation, and 24 weeks after enrollment and intervention initiation (at the end of the intervention period). The analysis will be conducted using a personal computer with Microsoft Windows 8.1 OS installed and IBM SPSS version 21.0 statistical software, with a two-tailed significance level of 5%.

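### Secondary endpoints are tested only by paired t-tests over time, which do not compare the randomised groups, although the protocol expects improvement compared with control

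*Protocol*

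**What the plan says.** The design is stated plainly in Research design: "This is a randomized, controlled trial conducted on two groups of patients".

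Statistical analysis methods then treats the two classes of endpoint differently.

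- **Primary, rates:** "Fisher's exact test will be used to compare the primary endpoints of temporary outpatient visit and readmission rates between groups".
- **Primary, counts:** "student *t*-test will be used to compare the number of temporary visits and readmissions between groups".
- **Secondary:** "Paired *t*-tests will be used to compare changes in secondary endpoints at baseline, 12 weeks after enrollment and intervention initiation", with the 24-week time point added in the same sentence. No comparison of arms is mentioned.

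All tests are two-sided at 5%.

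The secondary endpoints are SGRQ, EQ-5D, SCAQ, respiratory function, 6-minute walk distance, and steps and activity. The Overview, in its box on expected effects, says that the programme should "significantly improve the primary and secondary endpoints compared with the control group".

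For the activity meter, Secondary endpoints says that "the average number of steps taken and amount of activity will be collected from an activity meter at 12 and 24 weeks after enrollment". The Survey Schedule agrees: that row is blank at enrolment.

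**The concern.** A paired t-test asks whether a set of patients changed from one visit to another. The protocol's expectation for the secondary endpoints is a different one: that the intervention group does better than control. Practice on the walk test, regression to the mean, season and the attention that comes with being in a trial can move both arms together. A within-arm test counts that shared movement as change, and only a contrast between arms removes it.

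What is at stake is the interpretation of every secondary endpoint. If only the planned tests are run, the natural way to reach a statement about control is to set one arm's p-value beside the other's. That is not a test of the difference between arms, and its error rate is not held at 5%.

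**Working it through.** **1. Is there an arm contrast anywhere for these endpoints?**

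The two primary-endpoint tests are each described as between groups; the sentence on secondary endpoints is not. Under Allocation, participants are assigned from a random number table with facility as the adjustment factor. They are not matched one-to-one across arms, so the only pairing available is over time within a patient. No other section supplies a between-group analysis of a secondary endpoint. Running the paired test on all 34 patients together would not help either, since it also contains no arm contrast.

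**2. Steps and activity.**

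These are measured at weeks 12 and 24 only, and the intervention lasts 24 weeks (overview of the intervention program and observations). A paired test is possible for week 12 against week 24. It would miss any effect already present by week 12. A change from baseline cannot be computed.

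**3. Group size used below.**

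The protocol plans 17 per group, from a difference of 1.0 visit/year, SD 1.0, two-sided 5% and 80% power. Check: 2 × (1.960 + 0.842)² × 1.0² / 1.0² = 15.7 per group. Allowing for 10% dropout, 15.7 × 1.1 = 17.3, or 15.7 / 0.9 = 17.4. The planned figure reproduces to within one patient per group and does not bear on this point. It serves only as the n below.

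**4. How far can within-arm tests mislead?**

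Assumptions, none of them from the protocol: correlation 0.7 between the two visits, normal data, the same true shift of s SDs in both arms, and no programme effect.

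- SD of the change: √(2 × (1 − 0.7)) = √0.6 = 0.775, so the standardised change is d = s / 0.775.
- Chance p that one arm is significant: noncentral t with 16 degrees of freedom and noncentrality d × √17, two-sided 5%.
- Arms are independent, so the chance of significance in the intervention arm but not in control is p(1 − p).

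For s = 0.38: d = 0.38 / 0.775 = 0.49, noncentrality = 0.49 × 4.12 = 2.02, p = 0.477, and 0.477 × 0.523 = 0.249.

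| Shared shift s (SD) | p, one arm | Intervention arm only, p(1 − p) |
|---|---|---|
| 0 | 0.050 | about 5% |
| 0.1 | 0.079 | 7% |
| 0.2 | 0.171 | 14% |
| 0.38 | 0.477 | 25% |
| 0.6 | 0.850 | 13% |
| 0.8 | 0.979 | 2% |

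The product p(1 − p) cannot exceed 0.25 (at p = 0.5), so the 0.38 SD row is the ceiling. By symmetry, significance in the control arm alone is equally likely.

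**5. Sensitivity.**

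- With about 15 completers per arm, the figures for shifts of 0.2 to 0.6 SD run from 13% to 24%.
- With correlation 0.9 and 17 per arm, they are 24% at 0.2 SD, 8% at 0.38 SD and 0.1% at 0.6 SD.

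**6. Comparison with a between-group test.**

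A two-sample t-test on the change scores was simulated with 17 per arm, 100,000 trials and a shared change of 0, 0.25 or 0.5 SD of the change score. It was significant in 5.0%, 4.9% and 5.0% of trials. The shared shift cancels.

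**The case against.** The strongest reply is about weight. The formal hypothesis concerns temporary outpatient visits, and visits and readmissions are tested between groups. Neither the sample size nor the interim question of whether the main objective has been met rests on a secondary endpoint. The Overview wording is an expectation, not a hypothesis or decision rule. All of this stands. It limits the point to the secondary endpoints, but the Overview still shows that a comparison with control is intended.

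The sentence might also have been meant as a comparison of changes between arms. If so, the named test is wrong, because a paired t-test cannot compare two independent groups. Either reading needs correcting. Nor is this a detail left to a separate analysis plan, because the protocol names the method itself.

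A reader might infer more than the documents support:

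- **That a one-arm-only result will be reported as a programme effect.** No section says so.
- **That randomisation is lost for these endpoints.** It is not. Both arms are measured on the same schedule, so a valid comparison remains available from the planned data.
- **That no paired test of steps and activity can be run.** Week 12 against week 24 can be; what cannot be computed is change from baseline.

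**Conclusion.** The point holds for all secondary endpoints and only for them. The planned method contains no arm contrast, while the protocol's own expectation is one of improvement relative to control. This conclusion needs no numerical assumption.

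The size of the possible error does need assumptions. With 17 per arm, correlation 0.7 and no programme effect, significance in the intervention arm alone ranges from about 2% to 25% over shared shifts of 0 to 0.8 SD. It would be tempting to quote 25% as this trial's false-positive rate. That would be wrong: it is the mathematical maximum, it is reached only near one particular shift, and the protocol gives no SD or expected change with which to place any secondary endpoint on that scale.

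This should be fixed, but it does not threaten the primary analysis.

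**What to change.** In Statistical analysis methods, replace the paired t-tests with a between-group comparison of each secondary endpoint at 12 and 24 weeks, reporting the difference and its 95% confidence interval.

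- **SGRQ, EQ-5D, SCAQ, respiratory function, walk distance:** preferably ANCOVA of the follow-up value on group and baseline value, or one repeated-measures model. A two-sample comparison of change would also cure the defect. Include facility, the allocation factor, if numbers allow; with 34 patients, small sites may have to be pooled.
- **Steps and activity:** compare the groups directly at each visit.
- **Within-arm changes:** keep as description only.

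Cost: a change of analysis wording, with no new data, visits or patients. It is not free of process. Changes to the research protocol lists a change in the method of evaluating efficacy as an amendment, so Ethics Committee review may be needed.

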# Interim analysis and early termination of studies

An interim analysis will be conducted 12 weeks after the start of the intervention and enrollment to determine if the main objective has been achieved. The same methods of analysis will be used as for the main analysis. Even if the planned number of study participants is not attained as a result of the interim analysis, the study may be terminated early, if the superiority of the intervention group is deemed sufficient. The study will also be terminated if adverse events related to the intervention occur in 10% or more of the total number of participants.

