After Ethics Committee approval (May 2017) - March 2019

(3) Registration period

After Ethics Committee approval - October 2018

- 1. **Contact information**

(1) Eligibility criteria, treatment modification criteria, and other criteria requiring clinical judgment, registration procedures, and case record form (CRF) entry

Research Secretariat

Doctoral Program: [name]

Department of Cancer Nursing, Division of Family Support Nursing, Department of Health Sciences, Tohoku University Graduate School of Medicine

Tel: [name]

E-mail:　[contact]

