
The web-based program in the tele-nursing system consists of a patient site and a researcher site. The tablet terminal at the patient site has (1) a screen for recording daily physical condition, (2) a screen for video calls, (3) a screen for SNS input, and (4) a screen for respiratory rehabilitation information. The researcher's site will have (1) a list of the participant's telemonitoring data and (2) a screen for inputting comments. The researcher can check the participant's daily records and output the changes over time on a summary sheet.

The intervention period will be 24 weeks, and the number of ad hoc visits and readmissions during the past 12 and 24 weeks (primary endpoints) will be examined by the researcher at enrollment, 12 weeks after enrollment, and 24 weeks after enrollment, using the electronic medical record. At enrollment and at regular outpatient visits 12 and 24 weeks after enrollment, researchers will conduct a questionnaire survey about daily life, and perform respiratory function and 6-minute walk tests. In addition, activity meters will be checked 12 and 24 weeks after enrollment to collect data on the average number of steps and patient activity. Respiratory function and 6-min walk tests at enrollment as well as 12 and 24 weeks after enrollment will be performed by the researcher using equipment purchased using the research fund, since these tests are not covered by insurance and are outside the scope of usual medical care. Since the primary endpoints of this study are the number of emergency visits and rehospitalizations due to acute exacerbations of chronic respiratory diseases, the intervention will not be stopped in the event of worsening symptoms due to acute exacerbations. If the participant dies, the intervention is terminated because the study cannot continue. If a participant requests that the intervention be continued after their participation in the program, the intervention may be offered for an extended period of time, regardless of whether the participant is in the intervention or control group.

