# Evaluation items and methods

# Primary endpoints

Since the purpose of this study is to verify the effectiveness of a tele-nursing intervention program for the prevention of acute exacerbations of chronic respiratory diseases, it is necessary to set the status of acute exacerbations as an evaluation item. Acute exacerbations cannot be determined simply by considering the number of temporary visits and rehospitalizations separately, and thus, the primary endpoints of this study are the statuses of temporary outpatient visits (rate and number of visits) and rehospitalizations (rate and number of hospitalizations) due to acute exacerbations in the past 12 and 24 weeks, as well as the reasons for the outpatient visits or hospitalizations at enrollment (baseline) and 12 weeks after enrollment. The data will be collected from the patients themselves at baseline, 12 weeks after enrollment, and 24 weeks after enrollment. However, if the patient's complaint is unclear, it will be collected from the patient's medical record.

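### The 12-week superiority look can stop the trial on almost no data or on half the intervention period, and section 10.2 does not secure 24-week outcomes for those already randomised

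*Protocol*

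**What the plan says.** Section 10.2 of the protocol fixes the time of the look: "An interim analysis will be conducted 12 weeks after the start of the intervention and enrollment to determine if the main objective has been achieved". It adds: "The same methods of analysis will be used as for the main analysis". It then permits a superiority stop: "the study may be terminated early, if the superiority of the intervention group is deemed sufficient". The clause that introduces this permission shows that accrual need not be complete: "Even if the planned number of study participants is not attained as a result of the interim analysis". The section gives no minimum number of participants for the look, does not say whether the 12- or the 24-week window decides, and has no rule on collecting outcomes after a stop.

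Other sections set what has to be measured:

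- The section on the nursing program and observations sets a 24-week intervention. Primary endpoints covers temporary visits and "rehospitalizations (rate and number of hospitalizations) due to acute exacerbations in the past 12 and 24 weeks". The Survey Schedule lists both windows.
- The primary hypothesis (Research design, and section 9.2) is about visits over the intervention period.
- Section 11.1 has the CRF prepared after a participant's 24 weeks.
- Enrolment is sequential (section 8.1). The Overview sets registration as "After Ethics Committee approval - October 2018", with approval dated May 2017 and the research period ending in March 2019.
- Section 10.1 uses similar wording for each participant's own visits: "12 weeks after enrollment and intervention initiation, and 24 weeks after enrollment and intervention initiation (at the end of the intervention period").

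**The concern.** The look is meant to show whether the main objective has been met, yet it is placed halfway through the period that the main hypothesis covers. Its clock is also unclear. If the 12 weeks run from the opening of the trial, the look comes when hardly anyone can be scored. If they run from each participant's enrolment, the look has data, but only on the first half of the intervention. The section then does not say how many participants must have reached that point.

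A superiority claim from a trial of 34 could therefore rest on a handful of participants, or on 12-week counts alone. The 24-week outcomes of those still in follow-up could be left uncollected. This is separate from the repeated use of a 5% test: a stricter boundary would not supply 24-week data.

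**Working it through.** **Inputs.** Planned number 34, 17 per group (section 9). Registration from May 2017 to October 2018 (Overview): 17–18 months, or 73.9–78.3 weeks. The protocol states no accrual rate, so even accrual is an assumption. Planned effect 1.0 visit/year and SD 1.0 visit/year, two-sided 5% (sections 9.2 and 10.1).

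**The plan's own figure.** The protocol gives no interim number, information fraction or boundary to reproduce. For the total, the normal formula gives 2 × (1.96 + 0.84)² × 1.0² / 1.0² = 15.7, so 16 per arm. Allowing for 10% dropout, 16 / 0.9 = 17.8, so 18 per arm, close to the stated 17. I take 34 as given.

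**Trial-time reading (week 12 after the first participant starts).**

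- Enrolled: 34 × 12 / 78.3 = 5.2 to 34 × 12 / 73.9 = 5.5. The shortest window the dates allow (31 May 2017 to 1 October 2018, 69.7 weeks) gives 5.9. So about 5–6 participants, or 2–3 per arm.
- A full 12-week count exists only for someone enrolled at the outset, so essentially for the first participant. Nobody can have 24 weeks at any accrual speed.
- Person-time over 70–78 weeks of accrual is about 41 to 38 person-weeks out of 34 × 24 = 816, or about 5%. If accrual took 52, 26 or 12 weeks instead, the share would be about 7%, 12% or 26%.
- Even if all those enrolled could be scored, the smallest two-sided Fisher p with k per arm is 2 / C(2k, k). That is 2/6 = 0.33 for k = 2, 2/20 = 0.10 for k = 3 and 2/70 = 0.029 for k = 4.
- The t-test at the planned effect (1.0 SD) has power 9.5% with 2 per arm and 15.9% with 3.

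**Participant-time reading, look during accrual.** The protocol does not say how many participants must have reached 12 weeks. For a look or stop at trial week T, between week 24 and the end of an accrual window of w weeks:

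- enrolled = 34T/w, and completed 24 weeks = 34(T − 24)/w
- short of 24 weeks = 34 × 24 / w = 10.4 (w = 78.3) to 11.0 (w = 73.9), whatever T is
- at mid-accrual 17 are enrolled (week 37–39), so 10.4/17 = 61% to 11.0/17 = 65% lack the 24-week outcome

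As an example over 78 weeks, 17 participants have 12 weeks at 12 + 39 = week 51. About 22 are then enrolled, about 12 have 24 weeks and about 10 do not.

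**Participant-time reading, look after everyone's week 12.** A participant enrolled on 31 October 2018 reaches week 12 on 23 January 2019, after registration has closed. A stop then cannot shorten enrolment. About 29 of 34 would have 24 weeks and about 5 would not (78-week accrual, week 90).

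**Data flow.** On either clock, a participant at the 12-week point has no CRF yet, because section 11.1 prepares it after 24 weeks.

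**The case against.** The strongest reply is that 12 weeks is not an empty time point. Primary endpoints and the Survey Schedule name counts over both 12 and 24 weeks, so a participant with 12 weeks has a protocol-defined primary outcome. The Overview schema even shows a three-month program with the primary endpoint at three months. The first part stands. The schema conflicts with the 24 weeks in the program section and in sections 10.1 and 11.1, and these must be reconciled. As long as the hypothesis covers a 24-week intervention period, a 12-week count answers only half of it.

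Second, section 10.1 supports a per-participant clock. A look among those already at 12 weeks while accrual continues fits both sections. Section 8.1 expects a recruitment shortfall, which is another setting for the clause on the planned number. This stands: the trial-time result is one reading, not the only one.

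Third, the boundary and test details may properly sit in an SAP, and I do not raise them. But the protocol itself states when the look occurs and that the study may end on it. Whether randomised participants are followed afterwards is trial conduct.

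Four stronger conclusions are tempting but unsupported:

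- That a stop must end the study and leave participants short of 24 weeks for ever unscored. Section 10.2 says only that the study may be terminated and is silent on follow-up. Counts could still be obtained from participants or records.
- That the planned 5% test cannot reject at 3 versus 3. This is true of Fisher's test on rates, but the t-test on counts has no such floor, only low power.
- That those with 24 weeks are a self-selected subset. They are the earliest enrolled, and enrolment date is unrelated to arm under randomisation. The loss is of precision and of full-period outcomes.
- That the 10–11 participants are a share of 34. A stop during accrual means that fewer than 34 are randomised.

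**Conclusion.** The point holds as a defect in how section 10.2 is fixed. No reading of it yields a look that both has enough participants and addresses the full intervention period. On trial time, about 5–6 of 34 are enrolled and none has 24 weeks. On participant time, the decision can be scored but rests on half the period. In a stop during accrual after week 24, about 10–11 participants have 24-week outcomes that the protocol does not secure.

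The enrolment figures assume even accrual over 17–18 months. Faster accrual puts more people in the week-12 look, but still none with 24 weeks. The power figures take the planned effect and SD at face value and treat everyone enrolled as scorable, which is generous at that date. Because the stop is discretionary and the clock ambiguous, this should be corrected before any look is taken, but it does not show that the trial's final result is invalid.

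**What to change.** Rewrite section 10.2 in two parts.

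1. Tie the look to information on the 24-week endpoint, for example when 17 participants have completed 24 weeks, or drop the efficacy stop. With the same accrual assumption, 17 are enrolled by week 37–39 and complete at week 61–63, when 27–28 are enrolled, so a stop could still shorten enrolment. Amend section 11.1 if needed so that CRF data are available for the look.
2. State that an efficacy stop closes enrolment only, and that outcome data are collected to 24 weeks for every randomised participant before the final analysis. For a stop at week 61–63 this ends at about week 85–87, inside the May 2017 to March 2019 research period. Name one source for the counts: the program section uses the electronic medical record, while Primary endpoints uses the participant first and the record if the account is unclear. These should be reconciled.

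This concerns outcome collection and makes no proposal on treatment after a stop. The cost is time: the look comes about 50 weeks later than on the trial-time reading (61–63 minus 12 = 49–51), and a stop saves less. Otherwise it is protocol wording only.

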# Basis for setting

The primary hypothesis of this study is: A group of patients with chronic respiratory failure receiving NPPV with a tele-nursing intervention program (intervention group) will have fewer temporary outpatient visits (percentage and number of visits) due to acute exacerbations during the intervention period than a control group receiving only usual care (Figure 1). Based on the literature [24], we assumed that the average number of visits to the emergency department due to acute exacerbations of chronic respiratory diseases would be 2.4 visits/year for NPPV users and 1.6 visits/year for NPPV non-users to reduce the number of outpatient visits by 1.0 visit/year. The significance level, power of the study, and standard deviation of the number of improvement of visits are 5%, 80%, and 1.0 visit/year, respectively. In addition, assuming a dropout rate of 10% of the total number of patients, the intervention and control groups were calculated to require 17 patients each, for a total of 34 expected enrollees in both groups.

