# Methods of data management and self-inspection

# CRF preparation

The researcher will complete and correct the entries on the CRF. The investigator will complete the CRF promptly after the completion of the intervention for each participant. Since the program lasts for 24 weeks, the CRF will be prepared after 24 weeks of intervention. Care should be taken to ensure that the primary and secondary endpoints are covered and that vital signs and information on how the daily evolution of the participant's condition can be clearly and concisely ascertained. In addition, as with the nursing record, videophone information should be recorded such that it can be understood.

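### The 12-week superiority stop has no numerical boundary and no alpha set aside, so the t-tests on counts exceed the stated 5% type I error if that level applies at both looks

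*Protocol*

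**What the plan says.** Section 10.2 schedules one interim analysis at 12 weeks to see whether the study's main aim has been met. On method it says "The same methods of analysis will be used as for the main analysis". On the decision it says that "the study may be terminated early, if the superiority of the intervention group is deemed sufficient", and it allows this even when planned enrolment has not been reached. No p-value, boundary or spending function is given.

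Section 10.1 defines the methods carried over: Fisher's exact test for visit and readmission rates and Student's t-test for the corresponding counts, "with a two-tailed significance level of 5" per cent. No other level appears for the analysis.

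Section 9.2 sizes the trial without mentioning a look: "The significance level, power of the study, and standard deviation of the number of improvement of visits are 5%, 80%, and 1.0 visit/year, respectively". The target is "to reduce the number of outpatient visits by 1.0 visit/year", and after dropout "the intervention and control groups were calculated to require 17 patients each, for a total of 34 expected enrollees in both groups".

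**The concern.** The same hypothesis gets two chances of success. A trial that may declare superiority at 12 weeks, and otherwise tests again at 24 weeks at the full 5%, has a false-positive rate above 5% unless the level at one or both looks is reduced. Here neither is reduced, and the interim criterion is a judgement with no stated threshold.

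The estimate is also at stake. Results that trigger an early stop are selected for being large, so they tend to overstate the effect. In a trial of 34 patients the 12-week comparison would rest on few events, and stopping would forfeit the 24-week outcome around which the intervention period was set.

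**Working it through.** **Inputs.** From the protocol: two-sided 5% (10.1); difference 1.0 and SD 1.0 visit/year, power 80%, dropout 10%, 17 per arm (9.2); 24-week intervention with a look at 12 weeks. Assumed: the interim uses the same 5%; information fraction t = 0.5 (all patients at 12 of 24 weeks), varied from 0.25 to 0.9 because the protocol does not fix it.

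**Step 1. The plan's own figure.** n per arm = 2(1.960 + 0.842)² × (1.0/1.0)² = 15.70. Dividing by 0.9 for dropout gives 17.44, which the protocol takes as 17. Its figure is therefore that of a fixed design with one test at 5%.

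**Step 2. Error with two looks.** Under no effect, the interim and final statistics Z1 and Z2 are approximately bivariate normal with correlation ρ = √t. With c = 1.960:

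- Stop only in favour of the intervention, two-sided final test: error = P(Z1 > c) + P(Z1 ≤ c and |Z2| > c).
- Either direction counts at the interim: error = P(|Z1| > c) + P(|Z1| ≤ c and |Z2| > c).

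At t = 0.5, ρ = 0.707. The first is 0.0250 + 0.0416 = 0.0666. The second is 0.0500 + 0.0331 = 0.0831.

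| Information fraction | Favourable stop only | Either direction |
|---|---|---|
| 0.25 | 7.0% | 9.1% |
| 0.50 | 6.7% | 8.3% |
| 0.75 | 6.2% | 7.3% |
| 0.90 | 5.7% | 6.5% |

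The first column matches section 10.2, which mentions stopping only for superiority of the intervention.

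**Step 3. Check on counts.** Visit counts were simulated with no treatment effect, t-tests at 12 and 24 weeks, 15 or 17 per arm, and 200,000 runs per setting. The assumed rates were 1.6 and 2.4 visits/year, the two rates in section 9.2. Counts were Poisson or overdispersed (dispersion 0.5 and 1.0). With a favourable stop only, the overall error was 5.8% to 6.6%; with either direction, 7.0% to 8.3%. The final test alone gave 4.5% to 4.9%, so the excess comes from the look.

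**Step 4. The Fisher tests.** At the same visit rates with 17 per arm, Fisher's test at both looks, counting either direction, gave 3.6% to 4.0% overall. A single look at 24 weeks gave about 2% to 2.5%. The test is conservative enough at this size to absorb the second look.

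**Step 5. Events at 12 weeks.** If all 17 per arm had completed 12 weeks, at 2.4 visits/year in one arm and 2.4 − 1.0 = 1.4 in the other, the expected totals are 17 × 2.4 × 12/52 = 9.4 and 17 × 1.4 × 12/52 = 5.5. A look before full enrolment would have fewer.

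**The case against.** The strongest reply is that section 10.2 does not state a 5% interim level. It carries over the methods, and the level is inferred from section 10.1. The sponsor could apply a stricter standard: a favourable-only stop at p < 0.01 would give 5.2% overall at half information, which is hardly material. A separate analysis plan might also set a boundary. This stands as far as the size is concerned, so the figures are conditional on 5% carrying over. It does not remove the defect. The protocol creates an efficacy stop, gives a judgement as its only criterion and keeps the final test at full level, and nothing in it requires a stricter standard.

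Four stronger readings are tempting, and the document does not support them.

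- **An overall error of 8.3%.** This counts interim rejections against the intervention as well, and section 10.2 provides no such stop.
- **All primary tests exceed 5%.** Step 4 shows that the Fisher tests on visit rates do not.
- **A much larger figure across every primary test at both looks.** Most of that excess comes from having several primary tests, which is a separate matter. It also needs a readmission rate that the protocol does not give.
- **No usable data at 12 weeks.** Section 11.1 says "Since the program lasts for 24 weeks, the CRF will be prepared after 24 weeks of intervention", but the survey schedule and the primary endpoint section provide for collecting visits and readmissions at 12 weeks, and section 10.2 does not say that the look relies on CRFs. What remains is narrower: those data would not yet have had the CRF check against source documents.

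Nor does section 10.2 say who decides on stopping, so nothing can be concluded about whether that person or group is blinded.

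**Conclusion.** The concern holds in a limited form. The superiority stop is undefined and uncontrolled. If the 5% level applies at both looks, the t-tests on visit counts have an overall type I error of about 6% to 7%: 6.7% at an assumed information fraction of 0.5, and 5.7% to 7.0% over fractions from 0.9 to 0.25. The figure is about 8% only if an unfavourable interim result also counts. The visit-rate comparisons by Fisher's test stay below 5% under the assumed rates.

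The inflation is moderate. The further cost of a stop is a comparison based on some 15 expected events (9.4 + 5.5), under the protocol's assumed effect with everyone enrolled, and the loss of the 24-week result. The exact inflation cannot be fixed, because the timing in section 10.2 can be read per patient or by calendar and the stopping threshold is not stated.

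**What to change.** Amend section 10.2 in one of two ways.

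1. Delete the superiority stop and call the 12-week results descriptive. The 24-week test then keeps its full 5%.
2. Keep a stop, limited to one named primary endpoint, with a boundary fixed in advance. A Haybittle-Peto rule (two-sided p < 0.001 at 12 weeks, 0.049 at the final) gives 4.9% overall at half information. O'Brien-Fleming limits would also serve: at half information |Z| > 2.797 (p < 0.0052) at the interim and |Z| > 1.977 (p < 0.048) at the final. State whether 12 weeks is counted per patient or by calendar, since the O'Brien-Fleming limits depend on the information fraction.

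Under the second option, also require that 12-week data used for a stop are checked against source first, because section 11.1 defers the CRF to 24 weeks.

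The cost is a paragraph of protocol text and, if the stop is kept, an earlier data check. The first option gives up early stopping for efficacy; the second makes it unlikely.
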